## Abstract

**Background:**

The failures of recent studies intended to prevent cerebral vasospasm have moved the focus of research into delayed cerebral ischemia away from cerebral artery constriction towards other mechanisms. Recent accumulating evidence has suggested that early brain injury is also involved in the development of delayed cerebral ischemia, and that hydrogen can prevent early brain injury. Therefore, we have established a combination therapy of intravenous hydrogen infusion and intra-cisternal magnesium sulfate infusion for the treatment of both early brain injury and cerebral vasospasm. The present randomized controlled clinical trial is designed to investigate the effects of this novel therapeutic strategy on the occurrence of cerebral vasospasm, delayed cerebral ischemia, and clinical outcomes after high-grade subarachnoid hemorrhage.

**Methods:**

This study is a randomized, double-blind, placebo-controlled design to be conducted in two hospitals. A total of 450 patients with high-grade subarachnoid hemorrhage will be randomized to one of three arms: (i) Mg + H_2_ group, (ii) Mg group, and (iii) control group. Patients who are assigned to the Mg + H_2_ group will receive intra-cisternal magnesium sulfate infusion (2.5 mmol/L) at 20 mL/h for 14 days and intravenous hydrogen-rich fluid infusion (200 mL) twice a day for 14 days. Patients who are assigned to the Mg group will receive intra-cisternal magnesium sulfate infusion (2.5 mmol/L) at 20 mL/h for 14 days and intravenous normal glucose-electrolyte solution (200 mL) without added hydrogen twice a day for 14 days. Patients who are assigned to the control group will receive intra-cisternal Ringer solution without magnesium sulfate at 20 mL/h for 14 days and intravenous normal glucose-electrolyte solution (200 mL) without added hydrogen twice a day for 14 days. Primary outcome measures will be occurrence of delayed cerebral ischemia and cerebral vasospasm. Secondary outcome measures will be modified Rankin scale score at 3, 6, and 12 months and biochemical markers.

**Discussion:**

The present protocol for a randomized, placebo-controlled study of intravenous hydrogen therapy with intra-cisternal magnesium infusion is expected to establish the efficacy and safety of this therapeutic strategy.

**Trial registration:**

UMIN-CTR: UMIN000014696

## Background

Aneurysmal subarachnoid hemorrhage (SAH) accounts for 5% of all strokes [1]. The mortality rate is approximately 50%, and 20% to 30% of surviving patients have significant neurologic deficits [2,3]. In particular, high-grade SAH, which is classified as Hunt and Kosnik grades 4 and 5, accounts for approximately 20-40% of patients with SAH, and its prognosis is extraordinarily poor [4]. Delayed cerebral ischemia (DCI), a clinical diagnosis previously proposed by Vergouwen et al., is considered to be the most important cause of mortality and morbidity [5]. Angiographic cerebral vasospasm develops in approximately 70% of patients between 4 and 14 days after SAH, and the primary mechanism underlying DCI was widely believed to be cerebral vasospasm [1,6].

Numerous experimental and clinical studies have been conducted to prevent and/or treat cerebral vasospasm, and various prophylactic strategies against cerebral vasospasm have been advocated [7–12]. For example, magnesium sulfate has been studied as one of the most attractive therapeutic agents for decades [10–18]. Magnesium sulfate exhibits several beneficial effects such as vasodilation of vessels and attenuation of neuronal death. The mechanisms of these effects include blockage of the voltage-dependent calcium channels, inhibition of excitatory glutamate release, and interference with N-methyl-D-aspartate-glutamate receptors [19]. Several randomized controlled trials (RCTs) have been conducted to investigate the effects of intravenous magnesium sulfate administration on outcome after SAH [12–18]. However, these RCTs and meta-analyses showed that magnesium sulfate did not decrease DCI or improve the poor functional outcome after SAH [10–18].

Two main reasons for these negative results have been identified. Firstly, intravenous magnesium sulfate infusion results in only limited increases in cerebrospinal fluid (CSF) magnesium levels, whereas serious adverse events (such as bradycardia and hypotension) can occur at serum magnesium levels >2 mmol/L [20]. Therefore, these contradictory effects may be difficult to overcome for clinical use of intravenous magnesium infusion. Secondly, recent accumulating findings have suggested that early brain injury (EBI) is involved mainly in the development of DCI and causes the high mortality and morbidity observed after SAH [21,22]. EBI is the product of pathological mechanisms triggered in the brain during the first 72 hours after SAH. However, the time from the onset to initiation of intravenous magnesium administration was approximately 30–40 hours in most RCTs, whereas more time is required to achieve significant CSF magnesium levels after infusion [12,18,23]. This time latency can also be considered as one of the reasons for the negative results in RCTs.

Previously, we studied the safety and efficacy of intra-cisternal magnesium sulfate infusion and found that significant increases in CSF magnesium levels can be achieved without changes in serum levels [23–25]. However, the time latency from infusion to achievement of significant CSF magnesium level was also present with intra-cisternal infusion, and remains unresolved [23]. Theoretically, magnesium can also exert effects on EBI [21,22], but we consider that effective CSF magnesium levels are difficult to achieve during the period of EBI development, regardless of administration route. Therefore, other treatment strategies against EBI are more promising.

Increasing evidence has suggested that enhanced oxidative stress is involved in EBI as well as cerebral vasospasm following SAH [26–29]. Hydrogen can selectively reduce hydroxyl radicals and peroxynitrites, which are very strong reactive oxygen species that react indiscriminately with nucleic acids, lipids, and proteins, resulting in DNA fragmentation, lipid peroxidation, and protein inactivation [30–38]. Previous studies have shown that hydrogen has antioxidant, anti-apoptotic, anti-inflammatory, and cytoprotective properties that are beneficial to the cell [30]. Hydrogen is highly diffusible and could potentially reach subcellular compartments, such as the mitochondria and nuclei, which are the primary sites of reactive oxygen species generation and DNA damage [30,38]. In addition, hydrogen has no side effects, and we previously showed that hydrogen can be safely administered intravenously in patients with ischemic stroke [33]. Furthermore, recent experimental studies showed that hydrogen can alleviate EBI after SAH via attenuation of neuronal apoptosis [39–42].

These findings suggest that combination therapy using intravenous hydrogen infusion and intra-cisternal magnesium sulfate infusion may be effective to treat both EBI and delayed cerebral vasospasm. The present randomized controlled clinical trial is intended to investigate the effects of intravenous hydrogen therapy with intra-cisternal magnesium sulfate infusion on the occurrences of cerebral vasospasm and DCI, and clinical outcomes in patients with high-grade SAH.

## Methods

### Overview

This study is a randomized, double-blind, placebo-controlled trial to be conducted in two hospitals (National Defense Medical College Hospital and Mishuku Hospital) and includes three arms: (i) intravenous hydrogen-rich fluid infusion with intra-cisternal magnesium sulfate infusion (Mg + H_2_ group), (ii) intra-cisternal magnesium sulfate infusion only (Mg group), and (iii) placebo (control group). The protocol was approved by the ethics committee of the National Defense Medical College in May 2013 (#1126) and was registered on UMIN-CTR (UMIN000014696). The study follows the Declaration of Helsinki and good clinical practice guidelines. Written informed consent will be obtained from each patient or family members before inclusion in the study. The procedures performed during the study are outlined in Figure 1.

**Figure 1 Fig1:**
[figure not shown]
**Flow diagram.**

### Participants

All patients presenting with a diagnosis of SAH will be checked for eligibility by the treating physician. Inclusion criteria are: 20 to 80 years of age, aneurysm rupture, Hunt and Kosnik grade 4 or 5, aneurysm treated by surgical clipping within 72 hours after the onset, and written informed consent from the patient or family member. Exclusion criteria are: severe brain edema, heart dysfunction (New York Heart Association Class III or IV), renal insufficiency (calculated creatinine clearance rate of less than 30 mL/min), Fisher grade 4 with massive intracerebral hematoma, and rejection of randomization.

### Randomization

Patients who fulfill the eligibility criteria will be assigned to either the control group, Mg group, or Mg + H_2_ group by stratified block randomization, which will be carried out using a computer system by a statistician not related to the project team to protect the double-blind design and integrity of the study. Randomization will be stratified by sex, age (20–60 years and older than 60 years), Hunt and Kosnik grade, and Fisher group. The allocation ratio will be 1:1:1. Patients, treating physicians, and investigators assessing outcomes and analyzing data will be unaware of the allocation.

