### Interventions

All participating patients will be treated according to state-of-the art SAH management, comparable with recent published international guidelines [43]. During aneurysm clipping, a ventricular drainage tube will be placed in the lateral ventricle, and a cisternal drainage tube placed in the basal cistern. A spinal drainage tube will be placed in the lumber spine immediately after the clipping procedure. Fasudil hydrochloride (90 mg/day, 14 days) will be administered but not triple-H therapy. If severe cerebral vasospasm is detected by cerebral angiography at 7–10 days after surgery, fasudil hydrochloride (15 to 60 mg) will be administered via the proximal internal carotid artery [44,45].

Patients who are assigned to the Mg + H_2_ group or the Mg group will receive intra-cisternal magnesium sulfate infusion [23]. Figure 2 illustrates the irrigation system. Continuous infusion of 2.5 mmol/L magnesium sulfate in Ringer solution will be administered at 20 mL/h for 14 days. Irrigation will be performed through the cisternal to spinal drainage. The cisternal drainage tube and the pressure control system at 20 cm H_2_O will be connected by a T-connector for safe irrigation. The ventricular drainage and spinal drainage will be set at a pressure of 10 cm H_2_O and 5 cm H_2_O, respectively, which can be adjusted by the drainage volume. The respective drainage volumes will be checked hourly to avoid overdrainage or elevated intracranial pressure. CSF and serum magnesium ion concentrations will be measured daily until 14 days after surgery, but the principal investigators of the trial will remain unaware of the results. Patients assigned to the control group will receive continuous infusion of only Ringer solution at 20 mL/h for 14 days.

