### Sample size

Assuming that the incidence of DCI is 35% in the control group, 15% in the Mg group, and 5% in the Mg + H_2_ group, a total of 413 patients will be required (80% power and 2-sided α = 0.05). However, assuming approximately 10% loss to follow up, 450 patients will need to be recruited. Therefore, 150 patients must be randomized to each intervention arm.

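### Neither the allocation nor the named tests for DCI and vasospasm account for hospital in a two-hospital trial: no bias, but a small, avoidable loss of precision

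*Protocol article*

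**What the plan says.** The Overview describes a "placebo-controlled trial to be conducted in two hospitals" with three arms. Under Randomization, assignment is made "by stratified block randomization, which will be carried out using a computer system by a statistician not related to the project team", and the factors are listed: "Randomization will be stratified by sex, age (20–60 years and older than 60 years), Hunt and Kosnik grade, and Fisher group". The section adds: "The allocation ratio will be 1:1:1". Hospital is not among the factors.

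Statistical analysis plans an overall three-arm test for each outcome, followed by pairwise comparisons if that test is significant. For dichotomous outcomes it gives, as examples, Fisher's exact test or chi-square. It mentions neither a stratified test nor a hospital term.

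Sample size assumes DCI in 35% of controls, 15% of the Mg arm and 5% of the Mg + H2 arm, and concludes that "a total of 413 patients will be required (80% power and 2-sided α = 0.05"). Recruitment is then set at 450, or 150 per arm.

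Interventions leaves some room for local practice. Drainage pressures have starting values but may be changed, and for severe vasospasm "fasudil hydrochloride (15 to 60 mg) will be administered via the proximal internal carotid artery".

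**The concern.** With only two centres, hospital is a natural candidate for a prognostic factor. Surgery, drain management, intra-arterial rescue, Doppler recordings and the bedside detection of a new deficit all happen locally. If DCI or vasospasm is more common, or more often detected, at one hospital, then an arm that by chance holds more of its patients will show a different rate for reasons unrelated to treatment.

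Blocking within cells of sex, age, grade and Fisher group does not balance arms within a hospital, and a plain chi-square or Fisher test does not correct for the imbalance afterwards. The contrast most exposed is Mg + H2 versus Mg, because it has the smallest planned difference.

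**Working it through.** **Inputs.** From the protocol: two hospitals, 1:1:1 allocation, 150 per arm, DCI of 35%, 15% and 5%, two-sided α of 0.05, 80% power. Not in the protocol, and therefore assumed: the smaller hospital's share of patients (25 to 40%) and the gap in DCI between hospitals (10 or 20 points).

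**The plan's own figure.** Two proportions with unpooled variance, for the smallest contrast (15% versus 5%):

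n = (1.960 + 0.842)² × (0.15 × 0.85 + 0.05 × 0.95) / 0.10² = 137.36 per arm; × 3 = 412.07, rounded up to 413.

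The stated 413 is reproduced. It rests on Mg + H2 versus Mg, so that is the contrast against which to judge the size of this point.

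**Chance imbalance in hospital share.** SD of the difference in share between two arms = √(2p(1 − p)/150).

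- p = 0.25: √(0.375/150) = 0.050; × 1.96 = 9.8 points.
- p = 0.40: √(0.48/150) = 0.0566; × 1.96 = 11.1 points.

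**Shift in a pairwise DCI difference, 10-point gap in both arms.** 9.8 × 0.10 = 1.0 point; 11.1 × 0.10 = 1.1 points. Over wider splits (50:50, 70:30, 90:10) the 95% limit is 1.1, 1.0 and 0.7 points.

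**A 20-point gap.** Multiplying 11.1 by 0.20 gives 2.2 points, but this does not fit an arm with 5% DCI. At a 40% share, the largest gap with the smaller hospital worse is 0.05/0.40 = 12.5 points, reached when the larger hospital has no DCI in that arm. Even if the Mg arm keeps a 20-point gap, the limit is 1.96 × √(0.4 × 0.6/150) × √(0.20² + 0.125²) = 1.96 × 0.040 × 0.236 = 0.0185, or 1.85 points. At a 25% share the bound is 0.05/0.25 = 20 points, again only with no DCI at all at the larger hospital. If the smaller hospital is the better one, the bound falls to 0.05/0.60 = 8.3 or 0.05/0.75 = 6.7 points, so even a 10-point gap in both arms is generous.

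**Against the sampling error.** SE of the 15% versus 5% difference = √((0.1275 + 0.0475)/150) = 3.4 points, a 95% margin of ±6.7. The shift of about 1 point is a component of that margin, not an addition to it: (1.1/6.7)² is about 3% of the variance.

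**Type I error and power.** Simulated with 150 per arm, unadjusted two-sided α of 0.05 and 200,000 replicates per scenario. Without hospital stratification, the chi-square test had a type I error of 4.9 to 5.0%, and the Cochran-Mantel-Haenszel (CMH) test by hospital 5.0 to 5.1%.

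Power for 15% versus 5%:

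| Split; DCI by hospital in Mg; in Mg + H2 | Chi-square, hospital not stratified | CMH, hospital not stratified | Chi-square, stratified | CMH, stratified |
|---|---|---|---|---|
| 50:50; 10/20%; 3/7% | 84.2% | 84.6% | 84.6% | 84.9% |
| 50:50; 5/25%; 1/9% | 84.4% | 86.1% | 85.1% | 86.3% |
| 70:30; 9/29%; 3/9.7% | 84.4% | 85.8% | 84.9% | 85.9% |

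Changing only the analysis gains 0.4 to 1.7 points. Stratifying the allocation as well adds a further 0.1 to 0.3. Stratifying the allocation while keeping the unstratified test makes that test conservative: 4.4% type I error at a 20-point gap with a 50:50 split.

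**The case against.** The strongest reply is that nothing here is wrong. The scheme is a valid independent 1:1:1 randomisation, chance imbalance on a factor left out of it is already covered by the test's error rate, and the same could be said of any unstratified covariate. That stands. A reader might infer that leaving out hospital biases the comparison or inflates false positives; the simulation shows that it does not.

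Second, no section reports a difference between the hospitals, and much is shared: guideline-based management, a common infusion rate, starting drainage pressures, hourly volume checks, one imaging schedule, and neuroradiologist review of the CT images and angiograms. The drainage changes respond to the individual patient. Rescue follows the angiogram that triggers it, so it cannot alter that reading. This also stands: variation between hospitals is possible, not documented.

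Third, it is tempting to set a 2.2-point shift against the planned 10-point effect. The protocol's own 5% rate rules this out at the 40% share that produces the figure.

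Fourth, covariate adjustment is often left to a statistical analysis plan, which is not shown, and the protocol offers its tests as examples. If that plan already specifies a hospital-adjusted analysis, the point is met. As written, though, the protocol names tests that ignore hospital, and a better one is available from data in hand.

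**Conclusion.** The point holds as a minor improvement to the analysis. Hospital is neither balanced at allocation nor accounted for in the tests named for dichotomous outcomes. The consequence is a chance shift of about 1 point (95% limit) in a pairwise DCI difference, assuming a smaller-hospital share of 25 to 40% and a 10-point gap in DCI. A hospital-stratified test would gain about 0 to 2 points of power for 15% versus 5%, and nothing worth having if the hospitals do not differ. No figure can be given for vasospasm, because the protocol states no expected rate.

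The documents do not support a claim of bias, of an inflated error rate, or of known differences in practice between the hospitals. Nor do they show that hospital predicts outcome better than sex, so they give no ground for swapping one for the other in the allocation program of a trial that is already running.

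**What to change.** In Statistical analysis, replace the unstratified test for DCI and vasospasm with one that accounts for hospital. Examples are a CMH test stratified by hospital, or logistic regression with treatment, hospital and the randomisation factors. Use the same approach for the overall three-arm comparison and for the pairwise ones, and keep the planned multiplicity adjustment. If regression is chosen, one model across all three arms is safer than separate pairwise models: the assumed rates give 150 × (0.35 + 0.15 + 0.05) = 82.5 DCI events in total, but only 150 × (0.15 + 0.05) = 30 in the Mg + H2 versus Mg pair. Fix the choice before unblinding.

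The cost is a few lines of text; hospital is known for every patient and no new data are needed.

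Adding hospital to the allocation is optional. With four two-level factors (assuming two Fisher groups) it would raise the strata from 16 to 32, about 450/32 = 14 patients each, for a further 0.1 to 0.3 points of power in the scenarios above.

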### Interventions

All participating patients will be treated according to state-of-the art SAH management, comparable with recent published international guidelines [43]. During aneurysm clipping, a ventricular drainage tube will be placed in the lateral ventricle, and a cisternal drainage tube placed in the basal cistern. A spinal drainage tube will be placed in the lumber spine immediately after the clipping procedure. Fasudil hydrochloride (90 mg/day, 14 days) will be administered but not triple-H therapy. If severe cerebral vasospasm is detected by cerebral angiography at 7–10 days after surgery, fasudil hydrochloride (15 to 60 mg) will be administered via the proximal internal carotid artery [44,45].

Patients who are assigned to the Mg + H_2_ group or the Mg group will receive intra-cisternal magnesium sulfate infusion [23]. Figure 2 illustrates the irrigation system. Continuous infusion of 2.5 mmol/L magnesium sulfate in Ringer solution will be administered at 20 mL/h for 14 days. Irrigation will be performed through the cisternal to spinal drainage. The cisternal drainage tube and the pressure control system at 20 cm H_2_O will be connected by a T-connector for safe irrigation. The ventricular drainage and spinal drainage will be set at a pressure of 10 cm H_2_O and 5 cm H_2_O, respectively, which can be adjusted by the drainage volume. The respective drainage volumes will be checked hourly to avoid overdrainage or elevated intracranial pressure. CSF and serum magnesium ion concentrations will be measured daily until 14 days after surgery, but the principal investigators of the trial will remain unaware of the results. Patients assigned to the control group will receive continuous infusion of only Ringer solution at 20 mL/h for 14 days.

**Figure 2 Fig2:**
[figure not shown]
**Irrigation system.**

Patients who are assigned to the Mg + H_2_ group will receive intravenous hydrogen-rich fluid infusion. Hydrogen-rich fluid is produced using a non-destructive hydrogen diffusion apparatus (Miz Co., Fujisawa, Japan; Patent No. 4486157, Patent Gazette of Japan 2010) as reported before [23,33]. Bags of glucose-electrolyte solution (Soldem 1, 200 mL/bag, Terumo, Tokyo, Japan) are immersed, without opening or altering the bag, in a water tank in which water is electrolyzed periodically to produce water with hydrogen concentrations of up to 1.6 ppm. The concentration of hydrogen in the bag reaches saturation, increasing to more than 1.0 ppm, because of diffusion through the wall of the bag. Additional information describing this process can be found at: http://www.e-miz.co.jp/english/technology.html#non_destructivewebsite. Intravenous hydrogen-rich fluid (200 mL) will be administered at 200 mL/h twice a day (every 12 h). Patients assigned to the control group and the Mg group will receive glucose-electrolyte solution (Soldem 1, 200 mL) without added hydrogen at 200 mL/h twice a day (every 12 h).

If severe brain edema, heart failure, or renal failure occurs, the study intervention will be stopped immediately.

### CT, CT angiography, and CT perfusion

Head computed tomography (CT) will be performed on admission, and at 3, 7, 10, and 14 days after surgery. Head CT angiography will be performed on admission and at 7 days after surgery. Head CT perfusion will be performed at 7 days after surgery. All images will be reviewed by an experienced neuroradiologist to identify the occurrence of DCI and cerebral vasospasm.

### Digital subtraction angiography

Cerebral digital subtraction angiography will be performed on admission and at 7–10 days after surgery. Digital subtraction angiography will be reviewed by an experienced neuroradiologist to identify the occurrence of cerebral vasospasm.

